### Efficacy Analysis of Primary Outcomes

The efficacy of CAAT-PARK will be determined by comparing the mean change in values of the two groups from baseline to week 12 follow-up. Analysis between the two groups will be made using an independent sample *t*-test. Intention to treat (ITT) and per protocol (PP) analyses will be undertaken. For the intervention group, this is irrespective of their compliance with CAAT-PARK. ITT analysis will represent the primary analysis and will be used for evaluation of all outcomes. PP analysis will include patients who comply with the treatment as defined by completing five or more out of seven CAAT-PARK sessions. All participants will undergo sub-group analysis testing for potential effect modification for the presence of a spouse/carer on the treatment effect. Appropriate adjustments will be made in the statistical analyses for potential factors that are unevenly distributed between the groups. Specifically, participants with significantly high reported levels of cognitive impairment and anxiety and depression at baseline (assessed with the MoCA and HADS, respectively) will be analysed to determine the independent impact of these prognostic factors on the treatment effect. Adjusted estimates will be obtained by identifying baseline imbalances and incorporating these into a regression model using pre and post intervention primary outcome scores.

If normal distribution assumptions are not met, even after suitable transformations, non-parametric analysis will be adopted. Imputation for missing/incomplete data will be carried out using chained equations with all outcome measures and potentially correlated baseline values. A total of 10 imputed datasets will be created.

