### Sample Size

We will recruit a total of ninety-two family units (patient/carer pairs or patients alone), 46 per treatment group. This includes an additional 15% (n = 6) for potential participant attrition in each group. Where possible we aim to recruit patients with a spouse/carer, however, we will not exclude patient participants who do not have a spouse/carer but are wishing to participate. Using the primary outcomes, a pragmatic sample size of 40 participants per treatment group would provide an alpha of 0.05 and an 81% power to detect a difference of 25% improvement in medication adherence in the intervention group (detected by a one point shift in the MMAS-4) against 0% in the control group. This also provides 80% power to detect a Cohen's effect size of 0.69 in the PDQ-39, based on the published standard deviation of 8.89 in this patient group [43]. This would allow a difference in means of 6.13 (8.89 × 0.69) units in the PDQ-39.

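### The stated imputation variables omit randomised arm: if that list is the whole model, the treatment effect is pulled towards zero; carer scores need a separate rule

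*Protocol article*

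**What the plan says.** All the imputation text is in the Protocol article, Efficacy Analysis of Primary Outcomes. It gives the method and the variables, "Imputation for missing/incomplete data will be carried out using chained equations with all outcome measures and potentially correlated baseline values", and the number of datasets, "A total of 10 imputed datasets will be created". The same section defines the primary comparison as "comparing the mean change in values of the two groups from baseline to week 12 follow-up", tested as follows: "Analysis between the two groups will be made using an independent sample *t*-test". On the analysis set it says "ITT analysis will represent the primary analysis and will be used for evaluation of all outcomes". It also plans "sub-group analysis testing for potential effect modification for the presence of a spouse/carer on the treatment effect".

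Four other sections bear on the point:

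- Sample Size: "We will recruit a total of ninety-two family units (patient/carer pairs or patients alone), 46 per treatment group", of whom 6 per group are the attrition allowance. It adds that "we will not exclude patient participants who do not have a spouse/carer".
- Secondary outcomes: the Carer Distress Scale and a carer BMQ are listed among the outcomes.
- Follow-up Measurements: outcomes are collected at week 7 or 8 as well as at week 12.
- Randomisation: allocation is stratified by carer presence, and the statistician is masked to allocation.

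**The concern.** An imputation model should contain at least the variables of the analysis it serves. Arm is the only explanatory variable in the primary t-test, yet it is neither an outcome measure nor a correlated baseline value. If imputation is run on the listed variables alone, pooled over arms, each missing week-12 score is drawn as though treatment told us nothing beyond what the participant's observed scores already show. The completed data then understate the difference between arms. At stake is a loss of estimated effect and power in a trial of 92 units, caused by the handling of missing data and not by the therapy.

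The carer outcomes raise a different question. For a patient enrolled alone, carer scores are undefined, not missing. Chained equations over every outcome would fill them in unless told not to, and those values could reach the carer analyses.

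**Working it through.** **Inputs from the article (Sample Size).** 40 per arm plus 15% is 40 × 1.15 = 46, which reproduces the stated figure. Expected missing share: 6/46 = 13.0%. PDQ-39 target: 8.89 × 0.69 = 6.13, also as stated.

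**Inputs assumed.** Data missing completely at random; correlation 0.5 between baseline and each follow-up and 0.75 between week 7/8 and week 12; 30% of units without a carer. The article gives none of these.

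**1. Arm omitted, dropouts known only at baseline.** Randomisation balances baseline, so the imputed values differ between arms by zero on average:

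ratio to truth = (40 × 1 + 6 × 0)/46 = 0.870, that is 6.13 × 0.870 = 5.33 units.

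**2. Arm omitted, dropouts' week 7/8 scores observed.** Let k be the share of the week-12 effect already present at week 7/8, and b the slope of week 12 on week 7/8 after allowing for baseline, with arms pooled. Then ratio = (40 + 6bk)/46. In SD units, the within-arm residual variance is 1 − 0.5² = 0.75 and the residual covariance is 0.75 − 0.5 × 0.5 = 0.50. Pooling two equal arms adds k²d²/4 to the variance and kd²/4 to the covariance, where d²/4 = 0.69²/4 = 0.119.

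- k = 1: b = 0.619/0.869 = 0.712; ratio = (40 + 4.27)/46 = 0.962.
- k = 0.5: b = 0.5595/0.7798 = 0.7175; ratio = (40 + 2.15)/46 = 0.916.

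**3. Simulation.** 46 per arm, 13% missing, difference 6.13, SD 8.89, 10 normal-regression imputations, Rubin's rules, t-test on change at two-sided 0.05, 500 trials per cell (Monte Carlo error of each ratio 0.013-0.014).

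| Dropouts' week 7/8 scores | Formula, arm omitted | Simulated, arm omitted | Simulated, arm included | Power, omitted / included |
|---|---|---|---|---|
| Not observed | 0.870 | 0.868 (5.32 units) | 1.012 | 0.784 / 0.880 |
| Observed, half the effect | 0.916 | 0.903 (5.54 units) | 1.007 | 0.826 / 0.896 |
| Observed, full effect | 0.962 | 0.963 (5.90 units) | 0.992 | 0.882 / 0.882 |

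A separate simulation with a baseline correlation of 0.6 gave, with arm omitted, 0.862 from baseline alone, 0.918 with week 7/8 seen for half the dropouts, and 0.968 with it seen for all.

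The power column starts at about 0.88 and not at the stated 80% because 40 per arm at d = 0.69 gives 86% by t-test at two-sided 0.05.

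**4. Under the null.** With arm omitted and no week 7/8 data on dropouts, rejection was 0.029 against a nominal 0.05 (1,000 trials), so the error is conservative.

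**5. Carer variable.** A carer score was added to the chained equations and imputed for everyone, including the 30% with no carer (300 trials, Monte Carlo error 0.016-0.019).

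- Arm included: 0.988 without and 0.980 with week 7/8 scores.
- Arm omitted: 0.867 and 0.965, against 0.868 and 0.963 when there was no carer variable.

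The carer score therefore adds no visible attenuation to the patient endpoint.

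**The case against.** The strongest reply is that this is a condensed article. It spends one sentence on the imputation variables, does not call the list exhaustive, does not exclude arm, and does not say whether imputation is pooled or done within arm. Such detail often sits in a statistical analysis plan, and none is shown. This stands in part. A reader might infer that the plan as written biases the effect towards zero; the text does not support that, because it never says arm is left out. But the article does not leave the model open either: it names a variable set, and that set lacks the one variable the primary test depends on. The bias is therefore conditional, and the request to state the rule is fair.

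Second, the loss is modest where week 7/8 scores exist, and outcome measures can be read to include them. This stands and is built into the range above. Larger losses would need more missing data than the plan expects.

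Third, a reader might infer that imputing carer scores also drags the patient endpoints towards zero. The check found no such effect. Nor does the article say that scores will be imputed for absent carers; that follows only from a literal reading of the list.

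Fourth, a reader might extend the size of the loss to MMAS-4 or to the carer effect-modification test. Neither was computed. MMAS-4 is a short count with restricted entry scores, and carer presence could itself count as a baseline value. No figure is claimed for either.

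**Conclusion.** The point holds conditionally. If the listed variables are the complete imputation model, then at the planned 13% attrition the PDQ-39 difference is estimated at about 86-87% of its true value when dropouts have no post-randomisation data, and at about 90-97% when their week 7/8 scores are observed. In the worst of these cases power falls from about 0.88 to 0.78. Including arm removes the bias to within simulation error. The worst-case ratio follows from 40/46 and randomisation alone; the others depend on the assumed correlations and on how much of the effect shows by week 7/8. All assume data missing completely at random. The error works against the therapy and does not create false claims of benefit.

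The carer outcomes are a separate matter of definition: they should not be imputed where no carer exists, because the carer analyses could otherwise include invented values.

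**What to change.** Add to the imputation text:

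1. Imputation is carried out separately within each randomised arm, identified to the statistician only by a coded label so that masking is kept. Alternatively, every imputation equation contains arm, carer stratum and their interaction, which also matches the planned carer effect-modification test.
2. The Carer Distress Scale and the carer BMQ are imputed and analysed only among units with a carer, and are not used as predictors for patients without one.

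The cost is one or two sentences, settled before allocation is unmasked. No extra data, participants or visits are needed, so it is a free improvement.

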### Sample Size

We will recruit a total of ninety-two family units (patient/carer pairs or patients alone), 46 per treatment group. This includes an additional 15% (n = 6) for potential participant attrition in each group. Where possible we aim to recruit patients with a spouse/carer, however, we will not exclude patient participants who do not have a spouse/carer but are wishing to participate. Using the primary outcomes, a pragmatic sample size of 40 participants per treatment group would provide an alpha of 0.05 and an 81% power to detect a difference of 25% improvement in medication adherence in the intervention group (detected by a one point shift in the MMAS-4) against 0% in the control group. This also provides 80% power to detect a Cohen's effect size of 0.69 in the PDQ-39, based on the published standard deviation of 8.89 in this patient group [43]. This would allow a difference in means of 6.13 (8.89 × 0.69) units in the PDQ-39.

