### Description of Primary Measures

#### Morisky Medication Adherence Scale (MMAS-4)

The MMAS-4 is a self-report scale for identifying medication non-adherence [35] and has been used in PD [16,41]. The scale is constructed of four items answered by 'yes' or 'no'. Four 'no' responses signifies perfect adherence. Any 'yes' responses indicates some degree of non-adherence with medication. We aim to recruit people scoring two or more 'yes' responses.

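### The 81% power stated for MMAS-4 cannot be traced to the planned t-test on mean change, so the power of that analysis is unknown

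*Protocol article*

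**What the plan says.** MMAS-4 is the first of two primary outcomes. Its description reads "The scale is constructed of four items answered by" yes or no, so the score runs from 0 to 4, and entry requires a score of at least 2.

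Under Efficacy Analysis of Primary Outcomes, the groups are compared on mean change from baseline to week 12: "Analysis between the two groups will be made using an independent sample" t-test. A fallback is given: "If normal distribution assumptions are not met, even after suitable transformations, non-parametric analysis will be adopted". The article describes no responder or proportion analysis of MMAS-4.

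Under Sample Size, "a pragmatic sample size of 40 participants per treatment group would provide an alpha of 0.05 and an 81% power" for MMAS-4. The effect to be detected is "a difference of 25% improvement in medication adherence in the intervention group (detected by a one point shift in the MMAS-4) against 0" per cent under usual care. The same section quotes an SD for PDQ-39 (8.89) but none for MMAS-4 or its change. Recruitment is 46 per group: "This includes an additional 15% (n = 6) for potential participant attrition in each group".

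**The concern.** The power of a t-test on mean change depends on a mean difference and an SD. The MMAS-4 statement gives two percentages and no SD, which is the form of a comparison of proportions.

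The effect itself has two readings:

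- **Responder reading:** 25% of intervention patients move one point and no control patient does. The difference in mean change is then 0.25 × 1 = 0.25 point.
- **Mean reading:** the intervention mean moves one point, which is 1/4 = 25% of the scale, and the control mean does not move. The difference is then 1 point.

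These differ fourfold. A reader who wants to know what adherence effect 40 per group can detect cannot find out from the text, and the 81% may belong to a different test, a different alpha or both.

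**Working it through.** **Inputs.** From Sample Size: 40 per group, alpha 0.05 (taken as two-sided), 25% v 0%, stated power 81%; for PDQ-39, difference 6.13, SD 8.89, stated power 80%. From Efficacy Analysis: t-test on mean change. Assumed, because the documents give no figure: SD of MMAS-4 change 0.8 to 1.5.

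**1. Reproducing the 81% as two proportions.** Power = Φ{[d√m − z√(2p̄(1−p̄))] / √(p₁(1−p₁) + p₂(1−p₂))}, with d = 0.25, p̄ = 0.125, √(2 × 0.125 × 0.875) = 0.4677 and √(0.25 × 0.75) = 0.4330. Without continuity correction m = 40. With it, m = 40 × [1 − 1/(40 × 0.25)]² = 32.4.

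- Alpha 0.05, corrected: (1.4230 − 1.9600 × 0.4677)/0.4330 = 1.169, power 87.9%.
- Alpha 0.05, uncorrected: (1.5811 − 0.9167)/0.4330 = 1.534, power 93.8%. An exact Fisher calculation gives 95.7%.
- Alpha 0.025, corrected: (1.4230 − 2.2414 × 0.4677)/0.4330 = 0.865, power 80.7%, which rounds to 81%.

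So the figure is not reached at the stated alpha with 40 per group.

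**2. Cross-check on PDQ-39.** Normal formula: (6.13/8.89) × √(40/2) = 3.084. At alpha 0.025, Φ(3.084 − 2.241) = 80.0%, the stated figure. At 0.05, Φ(3.084 − 1.960) = 86.9%. Halving alpha over two primary outcomes would explain both figures, but the article states only 0.05. It is not the only candidate. With 34 per group (40 × 0.85) at alpha 0.05, the corrected proportion formula gives 80.3% and the PDQ-39 t-test 80.0%.

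**3. Power of the planned t-test** (40 per group, two-sided 0.05, noncentral t). Power of 81% requires a standardised difference of 0.64 (0.6425 unrounded). The SD of change would then have to be 0.25/0.6425 = 0.39 on the responder reading, or 1/0.6425 = 1.56 on the mean reading.

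| Assumed SD of change | 0.25-point difference | 1-point difference |
|---|---|---|
| 0.8 | 28% | 100% |
| 1.0 | 20% | 99% |
| 1.5 | 11% | 84% |

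**4. The responder scenario taken literally.** If each intervention patient moves one point with probability 0.25 and nobody else changes, the t-test is significant once 4 of 40 move: t = 0.10/√(0.10 × 0.90/39) = 2.08 against a critical value of 1.99. With 3 movers, t = 1.78. The chance of at least 4 when 25% are expected to move is 99.5%.

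**5. Sensitivity to the 0% control rate** (responder reading, alpha 0.05; corrected to uncorrected). 25% v 5% gives 60% to 72%. 25% v 10% gives 31% to 42%. Keeping the 25-point gap, 35% v 10% gives 68% to 77%.

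**The case against.** The best defence is that the text can be read as a mean-difference target. One point out of four is 25%, and 0% in control then means no average change, which agrees with the t-test. On that reading power is 84% or more over the assumed SD range, and 81% follows from an SD of 1.56. This stands in part. A reader might infer that the 81% cannot have come from a t-test, and the documents do not support that. What they support is that it cannot be traced to one, because the SD is absent. Condensing a protocol into an article might explain the omission, but the same paragraph gives the PDQ-39 SD and does not say which reading applies.

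The two-proportion origin is also inferred, since it needs an alpha that the article does not state. That weakens any claim to know how 81% was obtained. It does not rescue the figure, because the proportion calculation at the stated alpha and sample size does not give it.

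On the control rate, the documents hold no data. Eligibility uses a posted MMAS-4 and change is measured from a second MMAS-4 completed in clinic, which weakens the argument from regression to the mean. Ordinary retest variation on an unmasked self-report remains. The 0% is therefore optimistic and unsupported on the responder reading, but not shown to be impossible. On the mean reading the objection to it does not arise.

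A reader might also take the discrete 0-4 score as reason to replace the t-test or remove the non-parametric fallback. That is a matter of preference, and the point does not depend on it.

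**Conclusion.** The point holds as a fault in the stated power. The 81% does not describe the planned t-test at the stated alpha in any way the article allows a reader to verify. The two-proportion calculation that resembles it gives about 88-96% at alpha 0.05. The planned test gives anything from 11% to over 99%, depending on an unstated SD and an ambiguous target.

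It is tempting to conclude that the trial is underpowered for adherence, with power near 20%. The documents do not support that. The 20% rests on an assumed SD of 1.0 and the 0.25-point reading, while the literal 25% v 0% scenario gives over 99%. The true power is unknown. The t-test itself remains valid; what fails is the use of 81% as a benchmark for a null MMAS-4 result.

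**What to change.** In the Sample Size section:

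1. State whether the MMAS-4 target is a mean difference in points or a proportion of responders.
2. If it is a mean difference, replace the 81% with the power or detectable effect of the planned t-test at 40 per group, in MMAS-4 points with an explicit, sourced SD of change. Power of 80% corresponds to a standardised difference of 0.63 at alpha 0.05 or 0.70 at 0.025. Over an assumed SD of 0.8 to 1.5, that is about 0.5 to 0.95 point (0.634 × 0.8; 0.634 × 1.5) at 0.05, or 0.56 to 1.05 points (0.70 × 0.8; 0.70 × 1.5) at 0.025.
3. If a responder endpoint is intended, make it the stated analysis and power it with a justified, non-zero control rate.
4. State the alpha used for each primary outcome, for PDQ-39 as well as MMAS-4.

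The cost is wording and possibly a less favourable stated power. No extra patients are needed.

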### Qualitative Evaluation

Semi-structured interviews will be undertaken with a purposively selected sub-sample of patients (n = 10) and carers (n = 10) to explore the process and experience of receiving CAAT-PARK. Participants wishing to be interviewed will be pooled together and selected at random. This will ensure identification of participants wanting to be interviewed whilst preventing selection bias. Interviews will be thirty minutes in duration. The aims are to illuminate the quantitative findings by obtaining insight into the experience of receiving CAAT-PARK; consider which elements of CAAT-PARK are most helpful; explore perceptions of how CAAT-PARK has influenced medication taking; uncover potential barriers to receiving CAAT-PARK and explore how CAAT-PARK could be enhanced. All interview data will be audio recorded and transcribed verbatim. The transcripts will be coded using thematic analysis [50]. Analysis aims to ultimately inform the study outcome of patient acceptability of CAAT-PARK.

### Ethical Considerations

Although we do not anticipate any risk to study participants, we acknowledge the small possibility that increased medication adherence in PD may lead to greater incidence of dyskinesia. Dyskinesia is a common motor complication resulting from dopaminergic therapy in PD and will therefore be monitored by the TSC. It is theoretically possible that greater medication adherence may trigger drug induced psychosis, a rare but important complication of dopaminergic therapy in PD, so this will also be monitored in all participants receiving CAAT-PARK for its potential development.

The trial protocol and all related documents were given a favourable ethical opinion by Cambridge Central NHS Research Ethics Committee (REC reference number: 11/EE/0179).

## Discussion

Many people with PD do not take their anti-parkinsonian medications as prescribed. Sub-optimal adherence to prescribed medication in people with PD results in poor symptom control. This considerably impacts on QoL. Previous research has reported the benefit of various interventions including adherence therapy for improving medication adherence in other long-term conditions. Through the use of CAAT-PARK we aim to improve adherence behaviour in people with PD who are non-adherent to their prescribed medication. Furthermore, we aim to examine whether CAAT-PARK is effective for improving QoL in this patient group.

We have recently reported the effectiveness of adherence therapy in a trial of 136 hypertensive patients [51]. Improvements in medication adherence resulted in a substantial reduction in both systolic and diastolic blood pressures. Researchers have also tested the efficacy of other adherence intervention programmes in patients with psychotic disorders. One study showed people with psychotic symptoms in schizophrenia significantly improved after receiving a programme of adherence therapy [52]. Findings have shown similar adherence therapy interventions to provide direct benefit regarding service engagement and medication adherence [53]. Moreover, patient attitudes towards and satisfaction with medication improved in those who received treatment adherence therapy [53]. Such positive findings offer preliminary evidence of efficacy for the use of adherence interventions in people with long-term conditions and, furthermore, highlight patient acceptability of therapeutic adherence programmes.

Despite supportive findings, there is a paucity of randomised controlled trial evidence investigating the efficacy of interventions for improving medication adherence in people with PD. Findings from one study showed a 13% significant difference in timing adherence pre to post intervention between study groups after receiving simple didactic information relating to the continuous dopaminergic theory [54]. A recent study used a standardised eight week educational programme delivered to people with PD and their carers aiming to address psychosocial issues [55]. Findings showed an improvement in mood and less psychosocial problems and need for help in primary caregivers after receiving the intervention. Additionally patients improved in mood; however, there was only a trend towards significance in patients receiving the programme in relation to QoL [55].

The present study will use CAAT-PARK, a manualised intervention package that aims to ensure people with PD and their spouse/carers develop a vital understanding of the importance and personal benefit of sound medication adherence. Unlike previous studies, CAAT-PARK further recognises the importance of the spouse/carer for optimising medication adherence. Medication taking behaviour is a complex phenomenon in PD. A patient with PD may stop, omit doses, increase or decrease his or her medication based on the patient's perception of his or her own condition, the efficacy of the treatment, and his or her understanding of the indication for a particular drug, either accurate or fallacious. Discontinuing treatment secondary to actual or perceived adverse reactions, medication sparing (fear of becoming immune to treatment) and fear of long-term adverse effects of therapy have further been proposed [21]. Although didactic information has been shown to be effective we argue the importance of shared decision-making between patients and professionals, encouraging a dynamic and reflective process. With CAAT-PARK we attempt to identify and emphasise the personally relevant benefits to medication, which we argue will lead to positive behaviour change and resultantly improve medication adherence.

